### 2.4. Ethics and Dissemination

The protocol (Version 1.0) was approved by the Biological- Medical Ethical Committee of the West China Hospital of Sichuan University with approval No. 2023(2443) on 1 February 2024.

Written informed consent (see Supplementary File) will be obtained from all participants before we take images of the skin lesions and before we recruit them in clinical trials. The results of the project will be reported in a peer-reviewed journal.

### 2.5. Ethical Considerations and Data Privacy

This study complies with ethical guidelines for clinical research and data protection. All personal information, including clinical images, will be anonymized, with patient identifiers replaced by coded data. Only authorized personnel will have access to the linkage between codes and patient identities, stored separately in a secure database.

Sensitive clinical images will be stored on encrypted servers with restricted access, and data transmission will use encryption protocols to prevent unauthorized access. To minimize biases in AI-assisted decision-making, the algorithms will be trained on diverse datasets and monitored regularly for fairness and accuracy. An independent ethics committee will oversee any ethical issues related to AI use in clinical care.

Participants will be fully informed about data usage and their right to withdraw at any time. The study has received approval from the institutional ethics committee and complies with all applicable privacy regulations.

## 3. Discussion

We investigated the current situation of the AD patients and dermatologists in our clinic, recorded the visiting time for AD patients in our clinic, and found that if we evaluated a patient only with EASI, it would take an experienced dermatologist about 20 min. If we evaluated the patient with all the tools, including EASI, POEM, SCORAD, PP-NRS, DLQI, and ADCT, to see whether the T2T goal was achieved, at least 90 min would be needed. However, only 5 to 10 min could be allocated for each patient in clinic, and because there would be about 45 to 60 patients in 4 h of an outpatient visiting clinic, the patient’s medical and psychological needs would be far from met. Besides, due to the lack of knowledge of the disease, some of the patients use different medications randomly with eagerness for the rapid disappearance of the skin lesion or discontinue therapy when they feel that the symptoms have improved even a little bit without consultation with the doctor, and most of the AD patients have no idea about self-participation and clinician-patient combined management of AD, which make it difficult to control the disease or improve the clinical outcomes. It is crucial for both clinicians and AD patients to develop a convenient way to save time and have continuous management.

For the primary outcome, all five items including PP-NRS, EASI, SCORAD, POEM, and DLQI need to show improvement to meet the criteria for effective treatment as the primary outcome, and the goal of T2T could be regarded as achieved. These measures encompass both objective and subjective therapeutic effects, ensuring a comprehensive assessment of treatment efficacy. Improvement in each of these parameters is required to consider the treatment effective, with each criterion contributing essential information to the overall evaluation of treatment success.

This is an interdisciplinary project combining theories of clinical dermatology, computer science, and psychology and focusing on implementing a T2T framework for AD. Development of this app will be focused on patients’ participation in treatment, combination of evaluation from both patients and clinicians by applying different evaluation tools at different time points, improving the compliance of patients, and providing important an clinical decision-making basis for clinicians in order to maximize the integration and utilization of relevant resources to help patients achieve persistent control of the disease effectively and safely. According to “Expert Recommendations on Treat-to-Target (T2T) in the Systemic Treatment of Moderate to Severe Atopic Dermatitis” [6] published in August 2022 in China, the follow-up assessments are set at the time points of 2 weeks, 4 weeks, 8 weeks, and 12 weeks after treatment for evaluation of the short-term target goals and 6 months and 12 months after treatment to evaluate the long-term target goals (Figure 1). With the combinative assessment from both the dermatologists and the patients assisted by the app, the clinicians could determine whether the goals of T2T are met at the follow-up and how to proceed with the following treatment to achieve persistent control of AD.

The reliability of AI in evaluating cutaneous lesions remains a topic of debate, particularly in real-world clinical practice, where factors such as image resolution and the presence of artifacts can impact its performance. To mitigate these challenges, we plan to conduct rigorous external validation studies using a diverse set of images from various clinical settings, ensuring the robustness and generalizability of the AI model. These validation efforts will be complemented by expert reviews from independent dermatologists to confirm the system’s clinical relevance. Additionally, the AI system has been specifically designed to address cases where multiple dermatoses coexist in the same anatomical region, such as atopic dermatitis and acne on the face. Through advanced segmentation techniques and a multi-class classification approach, the system is capable of differentiating and accurately diagnosing individual lesions, even in complex presentations with overlapping skin conditions. This capability will be critical for ensuring accurate diagnoses and effective treatment recommendations in patients with multiple concurrent dermatological issues.

Since AD is a chronic disease, a key challenge in managing it through mobile application is ensuring long-term user engagement, and prolonged app use is important to improve adherence. To address this, the app will incorporate several strategies aimed at promoting sustained use. Personalization is central, with the app adapting content to the individual’s treatment progress and providing continuous feedback that encourages adherence. Additionally, gamification features, such as reminders, rewards, and goal tracking, are included to enhance user motivation and engagement. The app’s design is intuitive and user-friendly, specifically tailored to reduce cognitive load for users while maintaining ease of navigation. Periodic updates to the app, along with adaptive learning algorithms, ensure that the content remains relevant and responsive to evolving user needs. Moreover, the integration of support systems, including caregiver involvement and community engagement, provides a social support network that further encourages ongoing app use. These multifaceted strategies aim to create a sustainable, supportive environment that fosters long-term adherence, which is critical in the management of chronic conditions like AD.

The key strength of this study lies in the development of an innovative mobile application aimed at addressing limitations in the current management of atopic dermatitis (AD), particularly the time constraints in clinical settings and the lack of patient involvement. By enabling more comprehensive and efficient assessments, the AIADMS app has the potential to enhance treatment adherence and improve clinical outcomes. The app’s ability to streamline clinical workflows and provide real-time feedback empowers both clinicians and patients, fostering a more proactive approach to disease management.

However, several limitations should be acknowledged. First, the AIADMS app may face technical challenges, including issues related to accuracy, integration with existing clinical workflows, and potential difficulties with the user interface. These factors could affect both the usability and effectiveness of the app. Second, variability in patient adherence may influence study outcomes, as inconsistent use of the app might result in suboptimal disease management. Third, the study is conducted in a single center in China, which may limit its applicability to other populations with different healthcare systems and patient demographic or clinical characteristics, and generalizability of the results to other populations remains uncertain, given that the study focuses on a specific patient group. Further multi-centered studies involving diverse populations will be required to confirm the broader applicability of the AIADMS app. Additionally, a limitation of this study is the open-label, blinded end-point design, which makes it impossible to mask the assignment of participants. Both the participants and the investigators will be aware of group allocations, potentially introducing bias, particularly as participants in the AI-assisted group may have expectations of improved outcomes, which could influence self-reported measures, such as pruritus levels or the DLQI. To address this, the potential impact of the lack of blinding is being mitigated by having each participant’s condition evaluated by three clinicians to achieve a comprehensive assessment. Both groups will receive comparable levels of attention and care throughout the study, ensuring consistency in participant engagement. Additionally, objective outcome measures, including clinician-assessed severity of symptoms, will be incorporated to supplement self-reported data and provide a more comprehensive evaluation of treatment effects. Furthermore, all participants will be assigned unique identification numbers, with their individual data registered under these numbers. These data will be transferred to data collectors and statisticians who remain blinded to the group assignments, thus minimizing the risk of statistical bias during data analysis.

The study also relies on objective outcome measures like the Eczema Area and Severity Index (EASI), which offers standardized and quantifiable assessments of disease severity, reducing the influence of subjective judgment. Strict adherence to standardized treatment protocols and follow-up assessments across all groups will ensure consistency in care and data collection, minimizing variability and enhancing the reliability of the findings.

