#### 2.3.2. Randomization and Blinding

According to the sequence of time wherein the participants are enrolled, after entering the screen number and the individual’s information, the computer-based randomized number prepared on the Internet and the allocated group can be retrieved on the website of the CRS. While the statisticians responsible for final analysis will be blinded to the treatment assignment, the participants, investigators, healthcare providers, research assistants, and the responsible physicians will not be blinded.

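### The Discussion calls the trial a blinded end-point design, but section 2.3.2 blinds only the final-analysis statisticians and no masked endpoint assessor is described

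*Protocol article*

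**What the plan says.** **Design label.** In the limitations paragraph of section 3 (Discussion), the article writes that "a limitation of this study is the open-label, blinded end-point design, which makes it impossible to mask the assignment of participants". The next sentence concedes: "Both the participants and the investigators will be aware of group allocations, potentially introducing bias". It adds that expectations in the app arm are a concern "which could influence self-reported measures, such as pruritus levels or the DLQI".

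**Operative blinding rule.** Section 2.3.2 has one sentence on blinding. Its first half reads "While the statisticians responsible for final analysis will be blinded to the treatment assignment", and its second half reads "the participants, investigators, healthcare providers, research assistants, and the responsible physicians will not be blinded".

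**Safeguards offered.** The Discussion says that the lack of blinding is mitigated by "having each participant’s condition evaluated by three clinicians to achieve a comprehensive assessment". It does not say whether these clinicians are masked. It also says of the coded records: "These data will be transferred to data collectors and statisticians who remain blinded to the group assignments".

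**The endpoint.** Section 2.3.4 defines the primary outcome at 12 weeks on PP-NRS, EASI, SCORAD, POEM and DLQI. The Discussion confirms that a participant counts as a responder only if all five criteria are met. Sections 2.1.3 and 2.2 say that the model or app calculates all five scores from photographs and patient-completed questionnaire items.

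**The concern.** A blinded end-point means that whoever measures the outcome does not know the allocation. Section 2.3.2 provides masking only at the analysis stage, when the scores are already fixed. The label therefore claims a property that the operative section does not supply.

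At stake is how the primary result is read. In an open-label trial of an app, the main internal threat is that knowledge of the arm shifts the scores. A label implying that measurement is protected, followed by a mitigation that does not act on this bias, could lead readers to give the composite more credit than the design earns. Two of the five components, EASI and SCORAD, could be scored by masked raters, but as written nothing requires it. Masking cannot be added once the week-12 scores have been taken.

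**Working it through.** **Step 1. Who is masked at each stage.**

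| Stage | What the article says | Masked? |
|---|---|---|
| Self-report of PP-NRS, POEM, DLQI | Participants know their arm (2.3.2; Discussion) | No |
| Scoring of EASI, SCORAD | Three clinicians evaluate each participant (Discussion); 2.3.2 lists investigators, healthcare providers and responsible physicians as unblinded; 2.1.3 and 2.2 have the app calculate scores | Not stated; no masked rater described |
| Handling of recorded data | Data collectors receive coded records (Discussion) | Stated as masked, but after measurement |
| Final analysis | Statisticians (2.3.2; Discussion) | Yes |

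The stated masking begins after the endpoint has been measured.

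**Step 2. Self-reported components.** The Discussion names pruritus and DLQI as examples. POEM is patient-oriented by its full name in the Introduction. That makes three of five.

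**Step 3. Effect on the composite.** Response requires all five criteria, so any one component can decide a participant's status. With three components reported by participants who know their arm, the composite cannot be fully blinded, even if EASI and SCORAD raters were masked.

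**Step 4. What three raters achieve.** If each rater's error is a shared shift b from knowing the arm plus independent noise with variance s², the mean of three has expectation b and noise variance s²/3. The noise falls and b does not change.

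**Step 5. Reproducing the plan's own figure.** Inputs from section 2.3.5 are 35% versus 55%, 5% significance (sidedness not given; two-sided reproduces the figure) and power 0.80. With pooled variance and no continuity correction:

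n = [1.960·√(2·0.45·0.55) + 0.842·√(0.35·0.65 + 0.55·0.45)]² / 0.20² = (1.379 + 0.580)² / 0.04 = 95.9, so 96 per group.

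The final 116 per group is 96 × 1.20 = 115.2, rounded up. The sample size is not at issue here; it only sets n for the next step.

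**Step 6. Illustration of possible consequence.** Assume no true effect, 35% response in both arms, and a lift b in the app arm's composite rate caused only by knowledge of allocation. The article gives no value for b. With p₂ = 0.35 + b and p̄ the mean of the two rates, the chance of p < 0.05 in favour of the app is

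Φ{[b − 1.960·√(2p̄(1−p̄)/n)] / √[(0.35·0.65 + p₂(1−p₂))/n]}.

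For b = 0.05 and n = 116, this is Φ[(0.05 − 0.1246)/0.0635] = Φ(−1.17) = 12.0%.

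| Assumed lift b | n = 96 per arm | n = 116 per arm |
|---|---|---|
| 0 | 2.5% | 2.5% |
| 3 points | 6.3% | 6.9% |
| 5 points | 10.6% | 12.0% |
| 10 points | 29.2% | 34.2% |
| 15 points | 55.7% | 63.9% |

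For any lift above zero the error is larger at 116 than at 96. A bigger sample does not help.

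**The case against.** **The limitation is disclosed.** This stands. The label appears once, within a sentence about limitations. The next sentence admits that participants and investigators know the allocation, section 2.3.2 lists the unblinded roles, and the Conclusions concede that blinding is incomplete. Neither the Abstract nor the opening of section 2.3 uses the label. The fault is a wrong label and an ineffective mitigation, not concealment.

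**The three clinicians may be masked.** A reader might infer that everyone who measures the endpoint is unblinded. The documents do not establish that. It is a likely inference from the roles listed in 2.3.2, but the masking status of these three clinicians is not stated either way. What can be said is that no masked assessor is described.

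**Data collectors and research assistants.** A reader might also see a contradiction between masked data collectors in the Discussion and unblinded research assistants in 2.3.2. This is not shown. The collectors receive data already registered, and they may be different people.

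**The false-positive figures.** The assumed 5 to 10 points equal 25% to 50% of the hypothesised 20-point effect, and nothing in the article supports that size. The shift is in the whole composite. Bias on EASI or SCORAD changes a participant's status only if the other criteria are already met, and masking those raters would leave the self-report part untouched. The figures are not an estimate of the trial's error rate or of what masking would save. The article suggests a direction favouring the app only for self-reports; for EASI and SCORAD the direction is an assumption.

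**Masking is not free.** The Discussion puts one EASI at about 20 minutes for an experienced dermatologist, with 5 to 10 minutes available per patient. This bears on the cost, not on whether the label is right.

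**Conclusion.** The point holds as a contradiction between the Discussion and section 2.3.2. The article claims a blinded end-point, while its operative section masks only the final-analysis statisticians and no section describes a masked assessor. Three of the five required components are self-reported by participants who know their arm, so the composite cannot be fully blinded under any arrangement of raters. The three-clinician evaluation, as described, is not mitigation for lack of blinding.

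The count of three rests on POEM being patient-reported, which its name supports. The size of any bias is unknown, and the percentages in the working show only how sensitive the test is to an assumed shift. The documents do not support the stronger conclusions that all assessors are known to be unblinded, or that the false-positive rate is 12% to 34%.

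**What to change.** **Reconcile section 2.3.2 with the Discussion before week-12 scoring begins.**

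1. *Preferred.* State in 2.3.2 that the clinicians already planned who score week-12 EASI and SCORAD do not treat the participant, do not see the app record and do not know the allocation. State also that their scores, obtained the same way in both arms, are the ones entering the endpoint. The last clause is needed because sections 2.1.3 and 2.2 have the app calculate EASI and SCORAD, which leaves open which score counts.
2. *In either case.* Replace the blinded end-point label with an exact list of who is blinded and at which stage. Say that PP-NRS, POEM and DLQI, and therefore the composite, remain open to bias from knowledge of the arm.
3. *If masked scoring is not done.* Delete the label, and stop presenting the three-clinician evaluation as mitigation for lack of blinding.

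**Cost.** Items 2 and 3 are wording only. Item 1 uses clinicians already planned, and its small downside is scheduling raters who are independent of care. For scale, if each of three raters did a separate 20-minute EASI on all 232 participants, that would be 3 × 232 × 20 = 13,920 minutes, or 232 clinician-hours; the plan for three evaluators may already commit this time. Masked week-12 scoring also needs a 12-week assessment in the control arm, while section 2.3.3 leaves control follow-up times to the responsible dermatologist. That must be reconciled with the 12-week endpoint.

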## 4. Conclusions

In conclusion, despite the challenges posed by time constraints in clinical settings and the lack of full blinding, this study aims to improve the management of AD through the integration of advanced technology, patient engagement, and clinician oversight. By focusing on achieving treat-to-target (T2T) goals, we believe that the AIADMS app has the potential to facilitate more effective and safe long-term control of AD.

## Figures and Tables

**Figure 1 jcm-14-03015-f001:**
[figure not shown]
Target threshold at different time points in systemic treatment of moderate to severe atopic dermatitis under the treat-to-target concept [6,7,8].

**Figure 2 jcm-14-03015-f002:**
[figure not shown]
Design concept and fundamental function of artificial intelligence assistant decision-making system (AIADMS) in the form of an app and data interaction mode between healthcare providers and patients.

**Figure 3 jcm-14-03015-f003:**
[figure not shown]
SPIRIT schedule of enrollment, interventions, and assessments. ** List specific timepoints in this row.

**Figure 4 jcm-14-03015-f004:**
[figure not shown]
Study timeline and key milestones. The timeline outlines the major phases of the study from 2024 to 2029, including patient recruitment, image collection and labeling, AI model training, app design and development, app testing and optimization, app launch, and clinical trials and data collection. Each phase is represented across the respective quarters to illustrate the sequential progression and overlap of tasks throughout the study period.

## Data Availability

The datasets are not readily available currently. Individual participant data with anonymity will be uploaded to the IPD sharing platform to achieve data sharing. Data will be available after the agreement of the correspondence author upon reasonable request.

## Abbreviations

The following abbreviations are used in this manuscript:

AD	atopic dermatitis
AI	artificial intelligence
AIADMS	AI assistant decision-making system
T2T	treat to target
QoL	quality of life
EASI	Eczema Area and Severity Index
POEM	Patient-oriented Eczema Measure
PP-NRS	Peak Pruritus Numerical Rating Scale
SCORAD	Scoring Atopic Dermatitis
DLQI	Dermatology Life Quality Index
